# **BENEFICIARIES**

The direct beneficiaries of this study are all women who have anatomical pelvic organ prolapse. Their benefits include free screening for the symptoms and anatomical defects, free and early counselling and training for mild to moderate stages, and a referral system for advanced stages. The secondary beneficiaries of this study include health facilities, the community, and the families of the participants. This intervention will be provided at the early stage of POP, which reduces the risk of surgical management, which in turn reduces the resources and cost both for the family and the health facility. Moreover, we hope that in the long term, this information will provide an evidence-based treatment option for how best to correct prolapse for women in Ethiopia at a low cost.

# **COLLABORATORS**

This project needs the collaboration of different stakeholders to be effectively accomplished. Hawassa University, the home base of research teams, will review the protocol and provide ethical approval and some financial support of 60,000 Ethiopian birr (equivalent to 1,200 dollars). Most of the budget needed will be covered by the University of Minnesota, Maternal Health and the Worldwide Fistula Fund. The gloves and spatula needed to measure prolapse stage will be provided by the Ethiopian Hamlin Fistula Center. The Yirgalem Hamlin Fistula Center and selected health facilities will allow pelvic examination rooms and health professionals needed to examine study participants and provide training on PFMT (Table 3).

Table 3: Potential collaborators and their role for the study on Pelvic Organ Prolapse in Sidama Region, Ethiopia, 2022

|  | **Collaborators** | **Responsibility** |
| --- | --- | --- |
|  | Hawassa University | Provide Ethical Clearance |
|  |  | Provide study participants basic information from the database (HDSS) |
|  |  | Provide 60,000 ETB ($1200) for data collections |
|  |  | Assign senior research advisors |
|  | Sidama region health Bureau | Provide permission and support letter |
|  | Yirgalem Hamlin Fistula Center. | Provide patient pelvic examination site |
|  |  | Provide treatment for advanced-stage Prolapses |
|  |  | Assign and allow time for urogynaecologist to train and supervise the pelvic examination process. |
|  |  | Assign two trained health professionals to perform pelvic examinations. |
|  | Respective health centers | Provide patient pelvic examination site and materials |
|  |  | Assign two female Midwives/Nurses to train and counsel women on PFMT. |
|  | Health Extension workers | Remind and took patients to follow up site (health facility) |
|  |  | Counsel and convince participants to adhere to the training protocol |
|  |  | Support women to record pelvic exercises they performed |
|  | University of Minnesota | Provide financial support |

# **TIME TABLE**

Table 4: Time table indicating activity schedules for the study conducted on Pelvic Organ Prolapse in Sidama Region, Ethiopia, 2022

| Activities | Responsible person | April, 2022 | May, 2022 | Jun, 2022 | July, 2022 | Aug, 2022 | Sept, 2022 | Oct, 2022 | Nov, 2022 | Dec 2022 | Jan 2023 | Feb 2023 |
| --- | --- | --- | --- | --- | --- | --- | --- | --- | --- | --- | --- | --- |
| Ethical clearance | Hawassa University IRB |  |  |  |  |  |  |  |  |  |  |  |
| Preparation for data collection | Research team |  |  |  |  |  |  |  |  |  |  |  |
| Tool validation | Data collectors |  |  |  |  |  |  |  |  |  |  |  |
| Data collection | Research team |  |  |  |  |  |  |  |  |  |  |  |
| Report write up | Research team |  |  |  |  |  |  |  |  |  |  |  |
| **PHASE-II** | | | | | | | | | | | | |
| Pelvic Floor Muscle Training | Women and trainer |  |  |  |  |  |  |  |  |  |  |  |
| End-line Data collection | Data collectors |  |  |  |  |  |  |  |  |  |  |  |
| Data analysis | Research team |  |  |  |  |  |  |  |  |  |  |  |
| Report write up | Research team |  |  |  |  |  |  |  |  |  |  |  |

# **BUDGET**

Table 5: Budget Breakdown for the study conducted on Pe/vic Organ Prolapse in Sidama Region, Ethiopia, 2022.

| S. no | Item | Unit | Quantity | Cost/unit (ETB) | Multiplication | Total in ETB and (American Dollar) |
| --- | --- | --- | --- | --- | --- | --- |
|  | Ethical clearance | Proposal | 01 | 300 |  | 300 ($6) |
|  | Tool translation | Person | 02 | 359 | 5days | 3590($71.8) |
|  | Questionnaire duplication | Page | 20 | 2 | 857 | 34,280($685.6) |
|  | Data collection training | Person | 20 | 359 | 05 days | 35,900 ($718) |
|  | Hall rent | Room | 01 | 1000 | 03 days | 3000 ($60) |
|  | Refreshment | Person | 20 | 150 | 03 days | 9,000 ($180) |
|  | Transportation | Person | 20 | 100 | 2 round | 4000 ($80) |
|  | Trainer perdiem | Person | 02 | 1500 | 03 days | 9000 ($180) |
|  | Data collector perdiam | Person | 16 | 359 | 10 days | 57,440 ($1,149) |
|  | Women transportation | Person | 816 | 300 |  | 244,800 ($4,896) |
|  | Pelvic examiner | Person | 2 | 1500 | 30 days | 90,000 ($1,800) |
|  | Tool validation | Person | 2 | 300 | 50patient | 30,000 ($600) |
|  | Mask and Sanitizer | Person | 15 | 100 |  | 1500 ($30) |
|  | Speculum rent | Each | 816 | 20 |  | 16,320($326.4) |
|  | Sub-total 1 |  |  |  |  | **539,130 ($10,782.6)** |
|  | **PHASE**-II | | | | | |
|  | PFMT trainer | Person | 4 | 1000 | 10 days | 40,000 ($800) |
|  | Follow-up transportation | Person | 136 | 200 | 4 round | 108,800 ($2,176) |
|  | End line assessment | Person | 8 | 359 | 5 days | 12,565 ($251.3) |
|  | Supervisor per diam | Person | 02 | 359 | 40 days | 28,720 ($574.4) |
|  | Data entry (clerk) | Person | 02 | 359 | 10 days | 7,180 ($143.6) |
|  | Mobile card | Person | 15 | 200 |  | 3000 ($60) |
|  | Glove | Pack | 18 | 800 |  | 14400 ($288) |
|  | Spatula | Pack | 09 | 500 |  | 4500 ($90) |
|  | Pen and note pad | Each | 100 | 40 |  | 4,000 ($80) |
|  | Sub-total 2 |  |  |  |  | **223,165 ($4,463.3)** |
|  | Ground total |  |  |  |  | **762, 295 ($15,245.9)** |

****** $1 = 50 Ethiopian birr

# **ANNEX II: English Version Questionnaire**

**Hawassa University**

**College of Medicine and Health Sciences**

**School of Public Health**

**Part One: Respondent’s socio-demographic characteristics**

**Directions**

Ask the following questions one at a time and write the response on the space provided or encircle the appropriate response from the options listed. Allow the participant to take time to remember the correct answer when needed.

**Woreda_________ kebele________ Enumeration Area____________ Code_____ Mobile______________________**

| **Sr. No.** | **Questions** | **Response category** | **Skip to** |
| --- | --- | --- | --- |
|  | What is your current Age? | __________years completed |  |
|  | Where is your permanent place of residence? | 1. Urban 2. Rural |  |
|  | What is your current marital status? | 1. Never married 2. Married 3. Widowed 4. Divorced 5. Separated |  |
|  | What is your Religion? | 1. Ethiopian Orthodox 2. Protestant 3. Muslim 4. Catholic 5. Adventist 6. Other(specify)____________ |  |
|  | What is your main Occupation? | 1. Housewife 2. Farmer 3. Government employee 4. Nongovernmental employee 5. Private Business 6. Student 7. Others Specify)____________ |  |
|  | What is your Ethnicity? | 1. Sidama 2. Wolayta 3. Amhara 4. Gurage 5. Oromo 6. Other(specify)___________ |  |
|  | What is your level of education? | 1. Unable to read and write 2. Able to read and write without formal education 3. Primary Education 4. Secondary Education 5. Above secondary |  |
|  | What is your Husbands’ level of education?  Ask only if she is married (refer back to Q-103). | 1. Unable to read and write 2. Able to read and write without formal education 3. Primary Education 4. Secondary Education 5. Above secondary |  |
| **Part-II: Lifestyle Questions**  Ask the following questions one at a time and write the response on the space provided or encircle the appropriate response from the options listed. | | | |
|  | On average, for how long do you carry heavy objects/day (water, big baby, wood, stone, cereal, or grain) | -------- hrs |  |
|  | Have you ever smoked cigarettes? | 1. No 2. Yes |  |
|  | Do you have a family member who had Pelvic organ prolapse? | 1. No 2. Yes |  |
|  | Did you ever have a chronic cough (>3weeks) | 1. No 2. Yes |  |
|  | Did you ever have constipation (difficulty of defecation? | 1. No 2. Yes |  |
|  | Did you ever have a confirmed diabetes mellitus? | 1. No 2. Yes |  |

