POP also causes a vaginal bulge, voiding dysfunction, and sexual dysfunction which adversely affects the quality of life ([9](#_ENREF_9), [14](#_ENREF_14)). Sexual function is complex and may not be managed with surgery for POP. The relationship status and sexual desire might not improve by structural change (surgery) ([31](#_ENREF_31)). It was reported that sexual dysfunction like a disorder of sexual desire, arousal, and pain is common with a patient with anterior prolapse ([32](#_ENREF_32)).

Moreover, sometimes the treatment of POP by itself has different complications like infection, irritation, bleeding, pain, ulceration, and failure rate ([9](#_ENREF_9), [33](#_ENREF_33))

With these all complications (pain and severe difficulties carrying out daily activities), women with POP do not disclose it and refrain from seeking treatment. The disclosure is related to discrimination, stigma, and divorce ([27](#_ENREF_27)). Even in developed countries, women are ashamed of disclosing POP even to a health professional and suffer from the problem ([34](#_ENREF_34)). Almost 80% of POP patients from low-income countries were delayed at least for 12 months before seeking treatment even for severe degree prolapse ([26](#_ENREF_26), [35](#_ENREF_35), [36](#_ENREF_36)). POP is also a public health burden (beyond individual burden), it decreases the quality of life, increase the use of health care resource and decrease productivity ([37](#_ENREF_37)). Moreover, as a result of lifestyle modification, it is expected that the number of elderly population will increase from time to time, and the POP will become more prevalent shortly and increase economic and public health burden ([2](#_ENREF_2), [4](#_ENREF_4), [15](#_ENREF_15)). As its current status, the high cost for treatment and risk of recurrence after surgery makes POP both a health and financial burden ([2](#_ENREF_2)).

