Studies from developed countries show that obesity and overweight were associated with POP. The possible way in which obesity risks to POP is maybe through increasing intra-abdominal pressure ([7](#_ENREF_7), [8](#_ENREF_8), [77](#_ENREF_77)). Two systematic reviews and meta-analyses of papers from developed countries show that a higher body mass index > 24kg/m^2^ was a significant risk factor for primary POP ([17](#_ENREF_17), [78](#_ENREF_78)). A community-based study from East Lebanon and China also shows that a higher body mass index remains a significant risk factor for POP ([37](#_ENREF_37), [49](#_ENREF_49)). In contrast to the above findings, studies from Ethiopia show that lower body mass index (< 18kg/m^2^) was associated with POP ([38](#_ENREF_38), [56](#_ENREF_56), [79](#_ENREF_79)). It was justified that chronic under-nutrition may cause poor tissue tensile strength ([21](#_ENREF_21)). Two recently published systematic review and meta-analysis studies reported that there was no association between POP and BMI ([74](#_ENREF_74), [80](#_ENREF_80))**.**

1. **Family history (genetic) of pelvic organ prolapse**

Genetic predisposition may aggravate or impact POP development as the strength of collagen (the main component of connective tissue) that supports pelvic facia is determined by genetic factors ([4](#_ENREF_4)). In developed countries, the association between family history/genetics and POP was well researched. A population-based study that involved 4628 women diagnosed with POP and their families shows that the risk of developing POP is increasing with the number of family histories affected by POP. History of at least one first-degree relative has increased the risk of POP by two fold, and history of two first-degree relatives increased the risk more than three fold ([81](#_ENREF_81)). One systematic review and meta-analysis also show that on average, a positive family history of POP increases the risk threefold ([82](#_ENREF_82)). This is similar to a case-control study that revealed a family history of prolapse has remained associated with advanced prolapse ([83](#_ENREF_83)). Another study that assessed family history of POP among women who underwent gynecological surgery shows that family history has increased the risk ([84](#_ENREF_84)). A case-control study from Bahir-Dar also reported that a family history of POP was associated with POP ([56](#_ENREF_56)).

1. **Medical history**

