|  | Main material of the roof of the house? | 1. Natural roofing (no roof, mud, and sod) 2. Rudimentary roofing (rustic mat/plastic sheet, reed/bamboo, wood planks, and cardboard) 3. Finished roofing (metal/corrugated iron, wood, calamine/cement, ceramic tiles, roofing shingles) | | |  |
|  | Main material of the floor of the house? | 1. Natural floor (Earth/sand, dung) 2. Rudimentary floor (wood planks, and palm/bamboo) 3. Finished floor (parquet or polished wood, vinyl or asphalt strips/ plastic tiles, cement, ceramic tiles, carpet) | | |  |
|  | Does this household own any livestock, herds, other farm animals, or poultry? | 1. No 2. Yes | | |  |
| - - 1. 4 | How many of the following animals does this household own?  IF NONE, RECORD '00'.  IF 95 OR MORE, RECORD '95'.  IF UNKNOWN, RECORD '98'. | 1. Cows bulls_______________ 2. Other cattle______________ 3. Horses/Donkeys/Mules ____ 4. Camels________ 5. Goats _________ 6. Sheep _________ 7. Chickens/poultry ______ 8. Beehives ___________ | | |  |
| - - 1. 421 | Do you have separate rooms for cattle? | 1. Yes 2. No | | |  |
| - - 1. 422 | Does any member of this household own any agricultural land? | 1. No --------------------------------------- 2. Yes | | | 4.24 |
| - - 1. 423 | How many hectares of agricultural land do members of this household own? | ___________hectares | | |  |
| - - 1. 424 | Which of the following does your household have? (Multiple answers possible) |  | Yes (1) | No (0) |  |
|  |  | 1. Electricity---------- 2. Radio--------------- 3. Television --------- 4. Non-mobile telephone---------- 5. Computer ---------- 6. Refrigerator ------- 7. Table---------------- 8. Chair --------------- 9. Bed with spring matters------------ 10. Electric mitad ----- 11. Kerosene lamp/pressure------ 12. Lamp--------------- |  |  |  |
|  | Does any member of this household own: |  | Yes (1) | No(0) |  |
|  |  | 1. Watch -------------- 2. Mobile phone------ 3. Bicycle------------- 4. Motorcycle/scooter- 5. Animal-drawn cart- 6. Car/truck ------------ 7. Boat with motor----- 8. Baggage ------------ |  |  |  |
| - - 1. 426 | Does any member of this household have a bank account? | 1. No 2. Yes | | |  |
| - - 1. 427 | Does any member of this household have a micro finance account? | 1. No 2. Yes | | |  |

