**Gafa Mite: Dawaraanchote Dagoomittete Haja Xa’mi’nanni Borri-xa’mo**

Worada_________ Ollaa________ Dargu Kiiro____________ Koodde_____ Mobayle______________________

| **A.K.** | | **Xa’mo** | **Dawaro** | **Sai** |
| --- | --- | --- | --- | --- |
|  | | Dirikki me’’eho ? | __________wo’mu dirrinni wori |  |
|  | | Teessokki hiikkooti? | - - - 1. Quchumaho       2. Baadiyye |  |
|  | | Adhammete Gara | 1. Leexa 2. Adhantinota 3. shiidhinota 4. tidhantinota 5. baxxitinote |  |
|  | | Ammanokki hiitteeti?  (dawarokki qoqqowi? | 1. Ortodokise 2. Pirotestaante 3. Musiliime 4. Kaatolike 5. Wole xawisi____________ |  |
|  | | Loosu Qeecha? | 1.. Minaama (mini ama )  2. Baatto loossi’re galinoha   1. Mootimmate Loosaasincho 2. Mootimmannita ikkitinokki uurrinshara 3. Halanyaho 4. Rosaanchoho 5. Wole xawisi____________ |  |
|  | | Hiikko ayiddeeti?/ Hiitte gosaati? | 1. Sidaama 2. Wolayitta 3. Amaara 4. Guraage 5. Oromo 6. Wole xawisi___________ |  |
|  | | Rosikki deerri hiikkonneeti?? | 1. Nabbawanna borreessa didandeemma 2. Nabbawanna borreessa calla dandeemma 3. Umi dirimi rosaanchooti 4. 2^ki^ dirimi rosaanchooti 5. 5. 2^ki^ dirimi aleenni rosinote |  |
|  | | Gashshaniki rosi deerri hikkonneeti?  Adhantinota ikkituro,(xa’mo 103 buuxxi) | - - - 1. Nabbawanna borreessa didandaanno  1. Nabbawanna borreessa calla dandaanno 2. Umi dirimi rosaanchooti 3. 2^ki^ dirimi rosaanchooti 4. 2^ki^ dirimi aleenni rosinoho |  |
| **Gaamo-II: Heeshshote Gade Xa’minanni Borri-xa’mo**  Konni woroonni noo borri-xa’mo , xa’mitto/a gedensaanni taaltino dawaro qoqqowi | | | | |
|  | Mereerimunni, ayyirrinore me’’e saate bayiratta barrunni (waa, lowo qaqqo , haqqe, kinchonna gide | | -------- sate |  |
|  | Sigaara wiliishshite egennootta? | | 1. Dee’ni 2. Ee |  |
|  | Maatekki giddo otoottote ayyara gobbara higge fultinohu no ? | | 1. Dee’ni 2. Ee |  |
|  | Keeshshitino busano buuse egennota sase lamallara aleenni ? | | 1. Dee’ni 2. Ee |  |
|  | Jawa shumara ofolata woyte Fula giwanohenni? (fulate qarrissanno) | | 1. Dee’ni 2. Ee |  |
|  | Mundeekki giddo sukkaare noohero buuxi’rootta? | | 1. Dee’ni 2. Ee |  |

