|  | Minu galtinannihu ayeho? | 1. Ko meessiho 2. Baante gallanniho 3. Fiixunniho 4. Elunniho 5. Wole hee’riro xawisi_________________ | |  | |
|  | Konni mini giddo gonxanni kifilla me’’e no? | --------Kifilla no | |  | |
|  | Minu giddoydo iimiidi raga(korniise) mayinni biifinsoonniho? | 1. Kalaqamu haqqinni (biinfori dino, sabbunni,nna kandoonni sabbinni) 2. Calla anfi gede assinnoonniha (xu’minsoonnikki saattinni/plastic shara, shomboqqotenni/leemmichunni, haqqu xaawulinni, and komborsaatunni) 3. Xu’minsoonnikorniise (siwiilunni/culku siwiilinni, haqqunni,alumineemetnni/simintotenni | |  | |
|  | Mini uulliidi loosaminohu mayinniiti? | 1. Kalaqamunni noo gedeenni nooho (baatto/ bushshaho) 2. Safo tunge doogo hunnoonniho (haqqu xaawula, nna shomboqqotenni/ leemmichunni) 3. Xu’minsoonni mine (shakilunni) (haqqu xaawulinni xu’minsoonniha, uullano iimano shakila, simintotenni, alumineemetenni, uulla karranni shara(minxaafe) | |  | |
|  | Minu anni / ati saadate hoshsho, baatto hawuurranni saadanna lukkuwa ceo noosiho? | 1. Dee’ni 2. Eewa | |  | |
| - - 1. 4 | Aliidi saada giddonni minu annihu mageeshshaati?  Mitturi nokki ikkiro(00) wori.  95 tu woroonna aleenni ikkiro (95) wori.  Kiiro anfonikkiha ikkiro(98) wori | 1. Saadanna bootta_______________ 2. Wole saada______________ 3. Farado/harre/gaangootta ____ 4. Gaala________ 5. Me’’e _________ 6. Ge’reewo _________ 7. Caacurre/ lukkuwa ______ 8. Diishshote koshsha | |  | |
| - - 1. 421 | Saada galtannowi baxxino dargi noo’ne? | 1. Dee’ni 2. Eewa | |  | |
| - - 1. 422 | Maate’ne giddo loosi’nanni baatto afi’nohu no? | 1. Dee’ni ------------------------------------- 2. Eewa | | 4.24 | |
| - - 1. 423 | Minu annira me’’e hekitaare ikkitannoti loossi’nanni baatto noosi? | ___________Hekitaare | |  | |
| - - 1. 424 | Konni worooni noori giddo mini’ne giddo afamanohu hiiko neeti? (mittete aleeni doora dandiinanni) |  | Eewa(1) | Dino (0) |  |
|  |  | 1. Korreente---------- 2. Raadoone ----------- 3. Telewishiine -------- 4. Mine silke---------- 5. Kompiitere ---------- 6. Mitore qiissanno udiinnichi --- 7. Xarapheezzu -------- 8. Barcimu ------------- 9. Shiwote daallasi---- 10. Korreentete wolqanni sagale raisi’nanni mixashsho ----- 11. Laambunni/shaamu/ ------ 12. Faanoose------------- |  |  |  |
|  | Maatekki giddo togoo udiinni no: |  | Ee  (1) | Dino  (0) |  |

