**What causes pelvic organ prolapse?**

Prolapse is caused by a number of events that disrupt the vaginal support system. The factors linked to pelvic organ prolapse are mentioned below, along with a brief explanation of why they are linked.

**Pregnancy and childbirth**: This is the most prevalent cause, especially if the delivery was vaginal. The growing baby puts pressure on the pelvic organs and pelvic floor muscles, while hormonal changes through pregnancy lead the supporting ligaments to relax in preparation for birth. An episiotomy, a vaginal tear, or a forceps assisted delivery can weaken the supporting system, resulting in complications at the moment of delivery or later in life. Pelvic floor muscle workouts can help you maintain the strength of your pelvic floor muscles while you're pregnant.

**Obesity and being overweight**: the more weight your body has to manage, the more pressure is exerted on the pelvic organs and through the pelvis. A significant weight gain might place additional strain on the supporting structures, increasing the risk of prolapse.

**Heavy lifting**: If your day-to-day activities include heavy lifting or frequent bending, the increased abdominal pressure pushing downwards may raise the risk of a prolapse, especially if your pelvic floor supports are in sufficient.

**Family history**: A strong family history of pelvic organ prolapse, such as your mother or sister, may enhance your chances of developing a prolapse. This is assumed to be owing to a weak collagen type.

**Age**: As you get older, you're more likely to get a prolapse. Muscle strength may deteriorate as a result of aging, along with other changes.

**Menopausal changes**: As your levels of vaginal estrogen drop, some of the hormonal change that accompany menopause might exacerbate prolapse symptoms. The reduced amount of vaginal estrogen after menopause may impact prolapse symptoms.

**Constipation**: constipation and straining to empty your bowels might increase the risk of prolapse or worsen the existing prolapse. Increased intra-abdominal pressure is directed down onto the pelvic floor, causing strain and tension.

**Chronic cough:** If you have asthma or other illnesses that cause you to cough frequently, you may be at risk for a prolapse. This is caused to the pelvic floor being strained by recurrent increases in intra-abdominal pressure.

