**Marichooti otootto, helleenna ufuuffa sirote bisi kifilla widoonni gobba higge fultanno gede assannori?**

**Lowo korkaati no kuriuu abbannori,Sirote bisi kifilera lowo maali (xunchi) biso irkise amadannohu mimmituwiinni baxxa hanafirooti roorenkanni togoori ikkannohu.**

Godowa (godowu gata) nna qaaqqo ila: Roorenkanni godowanna qaaqqo sirote kifile widoonni ila abbitanno,qaaqqu godowamiro godowu giddo lophanni ha'ranno.Lophanni ha’ranno yannara sirote bissa aana lowo xiiwo kalaqanno.Hattono muje (hormone) godowu gatanno yannara cingiitanno gari soorramannohuraati ilate bisu kifilla qixxeessate kalaqamu ortenni. .

**Danna saino maqee lexxanna du’ma:** danna saino du’milli halli wori bisu kifiilla irkisanno maalira xiiwo ledirooti. .

**Ayirrinoricho bayi'ra/duha**:Ayirrinoricho barru barrunni bayi'ra bisinke aana qoldissanno(godowu maalira) xiiwo leddanno daafira konne qarra abbanno.

**Fiixaho kuni qarri hee'riha ikkiro:** lawishshaho muli fiixira (amakkira/rodookkira) tini mitiimma heedhuha ikkiro heedhara dandaanno.

**Diro**: diru lexxanni ha'ri kiiro tini mitiimma lexxitanno..

**Ilate yanna sa’'a** : ilate yanna sa'’a tenne mitiimmarano qarra abbitanno.

**Godowu moolle**: jawa shumara ofollinanni yannara godowu mooleenna niixa konni qarrira xaadisanno..

Keeshshitino buusano : Asimete dhibbi woy buusiisanno dhibbi konni qarrira tuganno.

Mudukku woroonni godowa dadhiniro:mudukku woroonni godowa dadhinirono konne qarra abbitanno(otootto dadha qarra leddanno.):

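### The family-history item does not say which relatives count and offers no *Don't know*, and its Sidaamu Afoo wording leaves the scope open between kin and household, so a listed Paper II risk factor may be misclassified.

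*Protocol*

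**What the plan says.** Annex II, Part-II (Lifestyle Questions) asks "Do you have a family member who had Pelvic organ prolapse" and allows only No or Yes. The Sidaamu Afoo form (Annex III, lifestyle items) reads "Maatekki giddo otoottote ayyara gobbara higge fultinohu no".

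The construct behind the item is described more narrowly elsewhere. Section 2.2 discusses family history under a genetic heading and reports: "History of at least one first-degree relative has increased the risk of POP by two fold". It also cites a review in which a positive family history raises the risk about threefold. The counselling leaflet (Annex IV) explains the factor as "A strong family history of pelvic organ prolapse, such as your mother or sister". Its Sidaamu Afoo version uses a kin term with the same two examples, "muli fiixira (amakkira/rodookkira".

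Family history of prolapse is a listed independent variable in Paper II (Study Variables) and a listed covariate in Papers III and IV (Variables). Paper II's measurement section defines heavy lifting and pelvic surgery but not family history.

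**The concern.** Three features of the item pull it away from the stated hypothesis.

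- **English scope.** The wording is not limited to blood relatives, so a respondent may count in-laws.
- **Sidaamu Afoo scope.** Interviews are held in this language. The item opens with the same two words as the wealth-index question "Maatekki giddo togoo udiinni no", whose English counterpart is "Does any member of this household own". A woman who hears the item as being about her household would leave out a mother or sister living elsewhere and could count a co-resident in-law.
- **No way to say she does not know.** Section 1.2 states that "women with POP do not disclose it and refrain from seeking treatment". Many respondents therefore cannot know whether a relative is affected, yet the only answers are No and Yes. Other items in the same questionnaire do offer a don't-know code, for example age at first delivery.

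At stake is one risk-factor estimate in Paper II, whose second objective is to identify risk factors. The Statement of the problem faults an earlier Ethiopian study for omitting this same factor. A poorly defined item cannot be repaired once the interviews are done.

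**Working it through.** **1. Text comparison**

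| Place | English | Sidaamu Afoo |
|---|---|---|
| Lifestyle item | family member | *Maatekki giddo* ... |
| Wealth index, goods owned | member of this household | *Maatekki giddo* ... |
| Wealth index, livestock, land area, rooms | household | *min-* stem |
| P-QoL (Part X), family-life item | family life | *maatekkira* |
| Wealth index, house owner | Family (answer option) | *Fiixunniho* |
| Leaflet, family history | mother or sister as examples | *muli fiixira*, with *ama-* and *rodoo-* |

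*Maate-* therefore covers both household and family. *Fiixa* is the word used where kin are meant. The lifestyle item uses the first, and nothing else in the item settles its scope.

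**2. What the plan calculated**

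The plan states no figure for family history. The survey size follows from prevalence alone: 1.96² × 0.563 × 0.437 / 0.05² × 2 = 756, and 756 / 0.93 = 813 (the 5-point margin is inferred, not stated). It is rounded up to 816. Family history is not a row of the risk-factor sample-size table and does not enter the trial sample size.

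**3. Misclassification of a 2×2 table**

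From the protocol: prolapse prevalence 56.3%, 816 women, 7% non-response, design effect 2, and a true odds ratio (OR) of 3 or 2, reading the cited threefold and twofold risks as odds ratios. Effective n = 816 × 0.93 / 2 = 379.4.

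Assumed, not in the protocol: true history in 15% of women; sensitivity (Se) 0.3-0.5; false-positive rate (F) 0-10% among women without a true history; errors equal in cases and non-cases.

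Solve 0.15·p1 + 0.85·p0 = 0.563 with OR 3. This gives p0 = 0.527 and p1 = 0.769. The true cell proportions are:
- cases: exposed a = 0.1154, unexposed b = 0.4476
- non-cases: exposed c = 0.0346, unexposed d = 0.4024

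The observed cells are A = Se·a + F·b, B = 0.563 − A, C = Se·c + F·d, D = 0.437 − C. The observed OR is AD/(BC). SE(log OR) = √[(1/A + 1/B + 1/C + 1/D)/379.4]. Power = Φ(log OR/SE − 1.96).

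- *Se 0.3, F 0:* A = 0.0346, B = 0.5284, C = 0.0104, D = 0.4266. OR = 2.69, SE = 0.584, power = Φ(−0.26) = 0.40.
- *Se 0.3, F 0.10:* A = 0.0794, B = 0.4836, C = 0.0506, D = 0.3864. OR = 1.25, SE = 0.312, power = Φ(−1.24) = 0.11.

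| Scenario, true OR 3 | Observed OR | Power |
|---|---|---|
| Perfect item | 3.00 | 0.91 |
| Se 0.3-0.5, F 0 (kin only missed) | 2.69-2.77 | 0.40-0.61 |
| Se 0.3-0.5, F 1-2% | 1.91-2.42 | 0.29-0.55 |
| Se 0.3-0.5, F 5-10% | 1.25-1.77 | 0.11-0.39 |
| Se 1, F 5-10% (in-laws counted, no kin missed) | 1.92-2.26 | 0.73-0.82 |

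For a true OR of 2, power starts at 0.61. It falls to 0.21-0.33 with kin only missed (observed OR 1.86-1.90), and to 0.07-0.20 with F 5-10% (observed OR 1.16-1.45). With 10-20% true history, Se 0.3-0.5 and F 5-10%, a true OR of 3 is observed as 1.18-1.88.

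**4. Unequal errors**

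If affected women know more about their relatives, for example Se 0.6 in cases and 0.3 in non-cases with no false positives and 10% true history, a true OR of 3 is observed as about 5.8. The bias then runs away from 1.

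**The case against.** **The form may mean family after all.** *Maate-* renders family life and appears in the partner item of the P-QoL, and several household items use the *min-* stem instead. A reader might infer from the parallel wording that the question is put to the wrong people. The documents do not support that: they show a word with two senses, and a co-resident mother or sister would count under either. This stands, and only a Sidaamu Afoo speaker can settle it. It does not remove the ambiguity, because no use of the word in the form marks blood kin.

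**Safeguards exist.** Translation is by a native speaker with maternal or reproductive health expertise, interviewers are fluent, and tools other than the POP-SS are pre-tested on 41 women, with unclear items modified. That helps, but the pre-test checks clarity and interview time. A question readily understood in the household sense could pass.

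**The attenuation depends on one assumption.** A reader might infer that the effect would shrink to nothing. That needs equal errors in cases and non-cases and a sizeable false-positive rate. At 5-10%, false positives make up 4.3-8.5% of all women (0.85 × 0.05 to 0.85 × 0.10), against 4.5-7.5% true positives (0.15 × 0.3 to 0.15 × 0.5). That is high if women conceal prolapse. This stands, so the low odds ratios are one scenario and not a forecast.

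**Narrow construct.** The threefold figure in Section 2.2 is for family history in general and not expressly first-degree, so an OR of 3 may be generous. The OR 2 results cover the first-degree figure.

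**Unknown is not coded No.** No instruction says so. A blank is possible, and Paper II plans multiple imputation. That is fair, but the printed answers leave the interviewer without a rule.

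**The trial is unaffected.** A reader might take the covariate role to mean that the treatment comparison is at risk. It is not: family history is one baseline covariate among many, and measuring it poorly weakens adjustment without biasing the randomised contrast.

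**Conclusion.** The point holds as one of ambiguous measurement. The item leaves open which relatives count, its Sidaamu Afoo wording can refer to family or household, and it gives no place for an unknown answer, although the hypothesis concerns first-degree relatives. The consequence falls on one listed risk factor in Paper II.

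Loss of power is the more robust effect. With 15% true history and 30-50% of true histories captured, power for a true OR of 3 falls from 0.91 to 0.40-0.61 even when the estimate barely moves (2.69-2.77). Strong attenuation, to 1.25-1.77 with power 0.11-0.39, needs an added 5-10% of false positives and equal errors in cases and non-cases. Unequal reporting could push the estimate upwards. All power figures are crude, before adjustment for other factors. True history, sensitivity and false-positive rate are assumptions that the protocol does not supply. This is worth correcting but is not critical to the trial.

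**What to change.** Before fieldwork, reword the item in both languages:

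- Ask whether her mother, a sister or a daughter has ever had pelvic organ prolapse, and state that blood relatives are meant.
- In Sidaamu Afoo, replace the *Maatekki giddo* opening with the kin wording already in the leaflet (*muli fiixa*, *ama*, *rodoo*). Have a Sidaamu Afoo speaker confirm how it is understood, or check it at the planned pre-test by asking respondents whom they had in mind.
- Add *Don't know* as a third answer, analysed as its own category or treated as missing, and never merged with No.
- Add the same definition to Paper II's measurement section, beside those for heavy lifting and pelvic surgery.

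The cost is one item reworded in two languages and one line of definition, with no extra contact or staff. *Don't know* will not reveal concealed prolapse in relatives, but it shows how often the answer is unknown.
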